**Primary outcome**		
Respondership	T1, T4	SWAN, SDQ

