### Data collection and management

Participants will only be identifiable via a unique code assigned at the date of inclusion to anonymize all data. Non-anonymous data such as informed consents will be stored in password protected folders and in a locker. We use the online electronic data capture software CASTOR EDC to collect and store questionnaire data. We also enter and store data in CASTOR EDC which is collected during an assessment at a Karakter or Triversum - GGZ-NHN location, such as physical measurements, COTAPP observation form and outcomes of the IQ test. These data then are stored in a locker. Video-data of the DB-DOS and Actigraph data will be anonymously stored on a network attached storage. Only appointed researchers have access to this storage. Data collected by the dieticians, such as information collected during weekly appointments with parents, are stored in Microsoft Access. Nutritional assessments (of three days) will be stored in password protected folders. Researchers will check the data collected by dieticians bi-weekly for completeness and discuss this with the dieticians. After completion of the study, all data will be entered again manually to compare the entered data in CASTOR EDC and to check for mistakes.

Parents and teachers only can continue to a different questionnaire if all items are completed. If questionnaires are not filled out on time, researchers will remind parents and teachers first via e-mail (twice) and then via telephone. Researchers will check which problems parents and teachers encounter in order to help them to complete the questionnaires. To prevent drop-out at the last assessment after 12 months, researchers will explicitly mention the duration of the participation of 1 year during the intake. If parents refuse to attend the last assessment, researchers will check whether parents want to participate in other measurements (e.g. Actigraph, online questionnaires, food diary, stool sample) without visiting a Karakter or Triversum - GGZ-NHN location, in order to collect as much data as possible. Parents can declare their travel expenses up to 25 euros. Children will receive at T0, T1 and T4 a small gift worth five euros. At the last assessment, parents receive an extra reimbursement of 25 euros. Participants may withdraw from the study for any reason at any time.

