### Statistical analyses

All primary analyses will be Intention To Treat. The primary outcome will be measured as an ordinal variable with five categories. Therefore, the effect of the intervention will be measured in terms of odds ratio, comparing odds for reducing ADHD symptoms and emotion dysregulation symptoms in the elimination diet group with the corresponding odds in the healthy diet group. Multiple logistic regression analyses will performed to compute the odds ratio and 95% confidence intervals, using ordinal logistic regression analysis. The CAU group will be used as a reference group.

Differences in continuous outcome measures between the dietary trajectories will be determined with analyses of ANCOVA. The follow-up value (T1, after five weeks) will be added as the dependent variable and the baseline value will be added as covariate. The two dietary groups will be compared on all outcomes at T1, using T0 scores as covariates. Clinical significance will be estimated using the partial eta squared effect. The CAU group will be used as a reference group.

In addition, a repeated measures ANOVA will be performed. First, the whole sample will be used (Intention to Treat) to determine whether adding a dietary treatment has beneficial outcomes on costs and effects of the whole treatment trajectory after 12 months (regardless of continuing the dietary treatment after 5 weeks or not). Next, per-protocol and post-hoc analyses will be performed using repeated measures ANOVA where the main outcome measures will be compared across the three conditions (i.e. elimination diet; healthy diet; CAU). Also, we will determine how many children adhered to the diet after 12 months, whether the intervention effects maintained after 12 months, which products are eliminated from the diet after 12 months and the nutritional quality of the attained diet after 12 months.

Finally, two moderator analyses will be performed: one comparing dietary responders versus non-responders (predicting respondership) and another comparing children/families adhering to a dietary treatment versus children/families that are not able to do so (predicting adherence). Both moderator analyses will be performed to compare children/families after 5 weeks and after 1 year of treatment.

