For the cost-effectiveness analysis, all cost data will be accumulated over the 12 months period. Cost differences between the two dietary conditions and CAU will be compared. Incremental cost-effectiveness ratios will be calculated by dividing cost differences between treatments by differences in Quality Adjusted Life Years, as estimated from EQ-5D scores. Uncertainty analysis using 5000 bootstraps will be performed and cost-effectiveness planes and cost-effectiveness acceptability curves will be plotted.

The impact of missing data on the outcome measurements will be evaluated using different methods, such as Last Observation Carry Forward (LOCF) and Multiple Imputation (MI).

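### The 12-month analysis is labelled whole-sample intention to treat, but the method named for it, repeated measures ANOVA, is complete-case by default

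*Protocol article*

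**What the plan says.** All references are to the protocol article; no separate analysis plan is shown.

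- **Method and analysis set.** After the ordinal regression for respondership and the ANCOVA for continuous outcomes at T1, Statistical analyses continues: "In addition, a repeated measures ANOVA will be performed". Its first use is "First, the whole sample will be used (Intention to Treat) to determine whether adding a dietary treatment has beneficial outcomes on costs and effects" over the 12-month trajectory, whether or not the child stayed on the diet after week 5. The same method then serves a second purpose: "per-protocol and post-hoc analyses will be performed using repeated measures ANOVA where the main outcome measures will be compared across the three conditions".
- **Missing data.** The end of the section says "The impact of missing data on the outcome measurements will be evaluated using different methods" and gives LOCF and multiple imputation as examples. It does not say that imputed data enter the main 12-month analysis.
- **Expected losses.** Data collection and management says "Participants may withdraw from the study for any reason at any time" and makes provision for parents who decline the last visit. No drop-out rate is stated anywhere.
- **Visits.** Respondership is listed at T1 and T4 (Table 3) and is built from SWAN and SDQ scores at T0, T1 and T4. Quality of life (EQ-5D), parenting stress, somatic complaints and sleep problems are scheduled at all five visits, and costs at T1 to T4.
- **Costs.** A separate paragraph accumulates costs over 12 months and uses 5000 bootstraps.

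**The concern.** Classical repeated measures ANOVA needs a full row of visits for each child. A child seen at T0 and T1 but not at T4 contributes nothing, and in a five-visit analysis neither does a child who missed only one online questionnaire. The label promises everyone, but the method keeps those who are complete.

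Two things are at stake on the 1-year aim. The first is precision, because children who were observed at T4 are discarded for a gap elsewhere. The second is bias. Children without a response at 5 weeks are advised to stop the diet (Study design, 2nd phase). They remain in the study, but their families may plausibly have less reason to return. Loss at T4 could then depend on the T1 result, which a complete-case ANOVA ignores and a model on all observed visits uses.

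Two smaller gaps sit in the same sentences. The effects to be analysed are not tied to named variables. Costs appear both under the ANOVA and under the bootstrap analysis, without a stated relation between the two.

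**Working it through.** **The plan's own figures.** The plan states no figure for the 12-month analysis. Its only power figures, 0.99 and 0.64 (Sample size and power), concern the ordinal regression of respondership. Simulating the proportional-odds test on the Table 4 counts gives 0.995 and 0.650, so they reproduce. They do not bear on this point.

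**Inputs.**
- From the protocol: 81 children per diet; modelled visits T0, T1, T4 (SWAN, SDQ) or T0 to T4 (five-visit outcomes).
- Assumed: T0 complete, and a fraction m missing at each post-baseline visit, independently between visits, with m = 5%, 10% or 15%.

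**Children kept per diet.**
- Observed at T4: 81 × (1 − m)
- Complete at T1 and T4: 81 × (1 − m)²
- Complete at T1 to T4: 81 × (1 − m)⁴

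**Excess standard error** of complete cases over the children observed at T4:
- Three-visit outcomes: √[(1 − m)/(1 − m)²] = 1/√(1 − m)
- Five-visit outcomes: √[(1 − m)/(1 − m)⁴] = 1/√(1 − m)³

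| m | Observed at T4 | Kept, T0/T1/T4 | Kept, five visits | Excess SE, three visits | Excess SE, five visits |
|---|---|---|---|---|---|
| 5% | 77 | 73 | 66 | 3% | 8% |
| 10% | 73 | 66 | 53 | 5% | 17% |
| 15% | 69 | 59 | 42 | 8% | 28% |

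For m = 10%: 81 × 0.81 = 65.6 and 81 × 0.6561 = 53.1; 1/√0.9 = 1.054 and 1/√0.729 = 1.171. For the whole planned sample of 162 + 60 = 222 children, 222 × 0.81 ≈ 180 would be kept for SWAN and SDQ.

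**Monotone drop-out.** If children who leave never return and 10% have left by T4, about 73 of 81 remain however many visits are modelled. That equals the number observed at T4, so no T4 value is thrown away. What is lost is the early data of those who left.

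**Bias.** The assumed scenario has no true T4 effect and a T1 effect of 0.4 SD. T4 loss is 5% among children who improved by T1. Among those who did not, it is 30% in one diet and 15% in the other. With correlations between visits of 0.4 to 0.6, simulated completers' change from T0 shows a false difference between diets of about 0.02 to 0.05 SD in absolute size, depending on the correlations and on which diet loses more. With the same loss rule (30% and 5%) in both diets it is about 0.01 SD. Regression on T0 and T1 removes it. For scale, the standard error of a difference between two groups of 81 is √(2/81) = 0.16 SD.

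**The case against.** The strongest reply is that missing data are addressed. Multiple imputation is named, and imputing before the ANOVA would keep every child; an analysis plan often settles which approach is primary. This stands in part: nothing says that imputation will not be the main approach. But the protocol fixes the main method and its label, and its missing-data sentence describes an evaluation of impact. Read as written, the 12-month analysis is complete-case unless something further is added.

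It is also fair that stopping the diet is not leaving the study. Non-compliant children are still assessed, and the protocol has reminders, a payment at the last visit and remote completion for those who decline it. Losses may therefore be low, and with no missing data the problem disappears. The 12-month analysis is also secondary to the 5-week comparison.

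A reader might infer more than the documents support:
- **That respondership is put through the ANOVA.** The text says "The primary outcome will be measured as an ordinal variable with five categories" and assigns it to ordinal regression in a paragraph that is not limited to T1, unlike the ANCOVA paragraph. The ANOVA's main outcome measures may simply be the SWAN and SDQ scores.
- **That ANOVA cannot take costs.** Costs are numeric at four visits, and the method needs no T0 value. Nothing says that visit costs would be averaged.
- **That the absence of a T0 value removes children.** It removes none.
- **That the precision loss at 10% missing is 11% and 23%.** Those figures compare with a trial without missing data (1/√0.81 and 1/√0.656), which no method can restore. Against the children observed at T4 the loss is 5% and 17%.

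**Conclusion.** The point holds in a limited form: the named method does not by default deliver the named analysis set, and the missing-data sentence does not close the gap. At an assumed 10% independent missingness per visit, the cost is about 7 children per diet (73 − 66) with T4 data discarded for SWAN and SDQ, and about 20 (73 − 53) for five-visit outcomes. This loss shrinks to none under purely monotone drop-out. The bias is likely to be small relative to the sampling error and rests on an assumed loss mechanism that differs between the diets. The protocol supplies no missingness rate, so all these sizes are illustrative. It is not established that the whole sample will fail to be analysed, only that the text as written does not secure it. The change is worth making because the better method is standard and needs no new data.

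**What to change.** In Statistical analyses:

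1. Name the continuous 12-month outcomes and replace the repeated measures ANOVA for them with a linear mixed model on all observed visits. Use visit as a category, treatment by visit, the T0 value as covariate and an unstructured covariance. Report the T4 contrast between elimination diet and healthy diet.
2. Keep multiple imputation as a sensitivity analysis and say so.
3. State that T4 respondership is analysed with the same ordinal logistic model as T1.
4. Remove costs from the ANOVA sentence, so that they are analysed only by the accumulated 12-month bootstrap already described.

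The cost is a few sentences of text and slightly more modelling work. No assessment, visit or sample size changes.

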#### 2nd phase: five weeks until 12 months after baseline

After 5 weeks, response to treatment is evaluated comparing measures of ADHD symptoms (i.e. SWAN questionnaire) and emotion dysregulation symptoms (i.e. SDQ questionnaire: dysregulation profile) before and after the 5 weeks (see Method section, primary outcome paragraph ‘respondership’). Full and partial responders (see primary outcome ‘respondership’) to the dietary treatment are invited to continue the diet in the second phase of the study until the end of the trial (12 months after baseline). Mixed responders (see primary outcome ‘respondership’) are offered to continue the diet, but are not explicitly advised as with the full and partial responders. To optimize the generalizability and feasibility of the study results to clinical practice, participants on the diet-trajectory are allowed to stop the diet switch to CAU after 5 weeks. This will be advised when participants do not respond to the diet (i.e. non-responders and deterioration group). Responders are allowed to add CAU to the diet, but this will not be advised as with the non-responders. Participants in the comparator arm will not be offered the possibility to switch to one of both dietary interventions to allow unbiased examination of (cost) effectiveness of the diet-trajectories.

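### If per-protocol means still on diet, the secondary 12-month three-group comparison sets diet groups selected on 5-week response against unselected CAU, which biases it towards diet

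*Protocol article*

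**What the plan says.** **Continuation rule** (Protocol article, 2nd phase: five weeks until 12 months after baseline). Response is judged from the change in SWAN and SDQ dysregulation scores over the first five weeks.

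- Full and partial responders "to the dietary treatment are invited to continue the diet in the second phase of the study".
- Mixed responders "are offered to continue the diet, but are not explicitly advised as with the full and partial responders".
- Diet participants may stop and move to CAU. On when this is recommended, the text says: "This will be advised when participants do not respond to the diet (i.e. non-responders and deterioration group".
- CAU works differently: "Participants in the comparator arm will not be offered the possibility to switch to one of both dietary interventions".

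**Analysis** (Protocol article, Statistical analyses). The 12-month repeated measures ANOVA is first run on the whole sample by intention to treat, "regardless of continuing the dietary treatment after 5 weeks or not". Then "per-protocol and post-hoc analyses will be performed using repeated measures ANOVA where the main outcome measures will be compared across the three conditions", the conditions being elimination diet (ED), healthy diet (HD) and CAU. The per-protocol set is not defined. The only non-compliance rule, under 1st phase: five weeks, covers the first five weeks.

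**Missing data** (same section). Their impact is to be examined by methods "such as Last Observation Carry Forward (LOCF) and Multiple Imputation (MI".

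**The concern.** The intention-to-treat step explicitly ignores whether the diet was continued. The natural reading of the per-protocol step that follows is therefore that it does not, and keeps only children still on their diet.

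On that reading, the two diet groups have been filtered on the 5-week value of the scales that make up the main outcome, while CAU keeps children whatever their 5-week course. Some of the early improvement that let a child through the filter is stable and some is chance. Any part that correlates with the 12-month score appears as a diet advantage even if the diet did nothing. CAU is also non-randomised, so randomisation gives no protection on either count.

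At stake is the reading of the 12-month on-diet results. Long-term effect is a stated secondary aim, and a figure for children who kept to the diet is the kind of result readers are likely to quote.

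**Working it through.** **The plan's own figures.** The plan states no figure for the per-protocol comparison. Table 4, which supplies the continuing shares below, is consistent with the stated power. With 81 per arm and two-sided 0.05, ordinal regression gives 0.993 to 0.996 for scenario 1 (stated 0.99) and 0.62 to 0.66 for scenario 2 (stated 0.64), depending on whether counts or percentages are used.

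**Inputs**

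- Full plus partial responders, scenario 1: ED 20 + 55 = 75%; HD 10 + 30 = 40%.
- Adding mixed responders: ED 75 + 12 = 87%; HD 40 + 25 = 65%.
- Full plus partial responders, scenario 2: ED 15 + 45 = 60%; HD unchanged at 40%.
- Overall responder share named in the stopping rule (Data monitoring): 42%.
- Group sizes: 81 per diet, 60 in CAU.
- Correlation *r* between 5-week and 12-month change: not in the documents, so assumed to be 0.3 to 0.7. A middle value of 0.5 arises when variances and correlations over time are equal, because both changes share T0: covariance (1 − ρ) divided by variance 2(1 − ρ) = 0.5.

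**Formula.** If the best fraction *q* on 5-week change is kept and there is no treatment effect, the kept children's mean 5-week change exceeds the group mean by φ(z)/q SD, where z is the cut with *q* above it. The expected spurious 12-month difference from an unselected group is r × φ(z)/q, in SD of 12-month change.

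| Kept | q | φ(z) | φ(z)/q | r = 0.3 | r = 0.5 | r = 0.7 |
|---|---|---|---|---|---|---|
| ED, full + partial, scenario 1 | 0.75 | 0.318 | 0.42 | 0.13 | 0.21 | 0.30 |
| ED, also mixed, scenario 1 | 0.87 | 0.212 | 0.24 | 0.07 | 0.12 | 0.17 |
| ED, full + partial, scenario 2 | 0.60 | 0.386 | 0.64 | 0.19 | 0.32 | 0.45 |
| HD, full + partial | 0.40 | 0.386 | 0.97 | 0.29 | 0.48 | 0.68 |
| HD, also mixed | 0.65 | 0.370 | 0.57 | 0.17 | 0.28 | 0.40 |

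**Advice only partly followed.** Suppose 20% of responders stop and 20% of the others continue. By simulation, the HD figure at 40% falls to 0.15, 0.27 and 0.37 SD for r = 0.3, 0.5 and 0.7. The ED figure at 75% falls to 0.08, 0.15 and 0.21 SD.

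**What this does to a test.** Simulation with no true effect, 42% of 81 kept (34 children) against 60 in CAU, two-sample t test of 12-month change, 4,000 runs. Results significantly in favour of diet, nominal rate 2.5%:

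| | r = 0.3 | r = 0.5 | r = 0.7 |
|---|---|---|---|
| Responders only kept | 26% | 59% | 89% |
| Advice partly followed | 11% | 22% | 41% |

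With all 81 kept, as under intention to treat, the rate is 2.7% and the mean difference 0.00 SD. The t test stands in for the planned ANOVA, so these rates show the order of the problem and are not exact.

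**ED against HD.** When the continuing shares differ, this randomised contrast is also disturbed. If neither diet has any 12-month effect but individual 5-week deviations persist, HD is filtered harder. It then gains r × (0.97 − 0.42) = 0.16 to 0.38 SD over ED under scenario 1, r × (0.97 − 0.64) = 0.10 to 0.23 under scenario 2, and r × (0.57 − 0.24) = 0.10 to 0.23 if mixed responders stay. But shares of 75% and 40% at one common threshold imply that ED is ahead by 0.674 + 0.253 = 0.93 SD at week 5. The kept children then average 0.93 + 0.42 = 1.35 SD (ED) against 0.97 SD (HD). Which diet looks better at 12 months therefore depends on how much of the early ED advantage lasts.

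**The case against.** **The set is undefined.** Stopping after week 5 is allowed, and for some children advised, so a child who switches as advised has arguably followed the protocol. On that reading this selection does not arise. An article may also leave the definition to the analysis plan. This stands, and it makes the point conditional. However, the per-protocol analysis would then largely repeat the intention-to-treat one, and the contrast between the two sentences points the other way.

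**The analysis is secondary.** This also stands. The primary analysis is at five weeks, and the 12-month whole-sample analysis comes before the per-protocol one. Neither has this selection, and the long-term aim does not rest on the per-protocol step alone.

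**The model is simple.** Respondership is a rule over six parent and teacher scales, not one normal score with a sharp cut, and *r* is assumed. The size is therefore uncertain. The direction of the bias is not: it favours diet for any positive *r*.

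**Missing data are partly covered.** A reader might infer that the analysis labelled intention to treat is really a completers' analysis. Repeated measures ANOVA by itself does use only complete cases, but multiple imputation is planned and could remedy this, so the text does not support that statement. LOCF is named as one of several ways to judge the impact of missing data, not as the main method. It also need not favour diet, since a non-responder's carried score is a poor one.

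**Conclusion.** The point holds in conditional form. If per-protocol means still on diet, the 12-month three-group ANOVA adds a bias towards diet over CAU. For r = 0.3 to 0.7 under Table 4 scenario 1, this is about 0.07 to 0.30 SD for ED and 0.17 to 0.68 SD for HD. The lower ends apply if mixed responders also continue. For HD the bias is somewhat less again if advice is only partly followed. Scenario 2 would put ED at 0.19 to 0.45 SD when only full and partial responders stay. These figures rest on an assumed correlation, a normal 5-week change and no true effect.

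Two stronger readings are not supported. A reader might infer that the analysis will show the diets to be better than CAU. The bias has a known direction, but the observed result also depends on the true effect of CAU, which is active guideline treatment in a non-randomised group, and that cannot be predicted. A reader might also infer that HD will look better than ED. The contrast may be distorted, but its direction depends on whether the 5-week ED advantage persists, which the documents do not say.

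This should be changed before analysis. It does not threaten the primary result.

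**What to change.** 1. Base the 12-month comparison on all children by assigned group, with ED versus HD as the main randomised contrast and CAU as a non-randomised reference.
2. Replace repeated measures ANOVA with a linear mixed model on all observed visits, so that a child with one missed visit is not lost. This does not cure the selection; keeping all children by assigned group does.
3. Do not test an unadjusted on-diet group against CAU. Either estimate an ED versus HD adherer effect with inverse-probability weights for continuation built from T0 and T1 data, or report on-diet results as descriptive.
4. Define the per-protocol set. If switching as advised is not meant to count as a protocol deviation, say so.
5. Keep multiple imputation and drop LOCF. Respondership is measured only at T1 and T4, so LOCF would carry a 5-week on-diet score to month 12 for children who may have stopped.

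The cost is analysis wording and code. Non-compliant children are already due for follow-up, so no new data collection is needed. The downside is that there is no simple confirmatory figure for adherers only. The weighted estimate will also be imprecise if few children with a poor 5-week response stay on their diet.

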To address these issues, the ‘Treatment of ADHD with Care as usual versus an Elimination diet’ (TRACE) study has been developed. This is the first RCT (two armed, 50:50 ratio) to determine the short- and long-term effectiveness and cost-effectiveness of an ED compared to an active control group (a healthy diet). Care As Usual (CAU) is included as a comparator arm. During the initial 5 weeks of the study, participants receiving a dietary treatment are not allowed to start any other treatment. Also, medication prior to the dietary treatment has to be discontinued no later than 1 week before start of the diet. The study will examine effects on both ADHD and emotion dysregulation, given that an ED showed equal effects on ADHD and its common comorbidity Oppositional Defiant Disorder (ODD) (i.e. children with ODD are more likely to experience emotion dysregulation problems) [14]. We will substantially improve upon previous studies by comparing an ED with a healthy diet (based on the World Health Organization (WHO) guidelines), comparing the two dietary treatments with CAU, examining the short- and long-term effects (i.e. after 5 weeks and 1 year) and cost-effectiveness, measuring the nutritional quality of the consumed diets and including blinded and objective measurements.

The primary objective of the TRACE study is to quantify the short-term (after 5 weeks) effectiveness in reducing ADHD and emotion dysregulation symptoms of an ED compared to an active control group (a healthy diet) in children aged 5–12 years with ADHD: we assume that the ED is more effective than the healthy diet. Secondary, the study aims at examining the long-term (after 1 year) effects in reducing ADHD and emotion dysregulation symptoms. Moreover, the study aims at examining the short- and long-term effects of an ED compared to an active control group (a healthy diet) in reducing secondary outcome measures related to ADHD such as cognitive outcomes, motor activity and sleep pattern. In addition, the study aims to identify potential moderators and mediators (e.g. socioeconomic status (SES), ethnicity, comorbidity) of the short- and long-term response to dietary treatments, and to examine the nutritional quality of the attained diet and health of children treated with a dietary treatment compared to CAU. Finally, the study aims to examine the cost-effectiveness of the dietary treatments compared with CAU.

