### Study design

#### Randomization

Originally, the TRACE study was a three arm randomized controlled trial: participants were randomized to an elimination diet, healthy diet or CAU. However, randomization across a dietary intervention versus CAU proved not feasible. Parents usually had a strong preference towards either a dietary intervention or CAU. This resulted in an extremely slow inclusion rate, a high number of drop-outs and thereby unrepresentative groups of CAU. Therefore, after inclusion of 17 participants, the design was changed into a two arm randomized controlled trial (elimination diet vs. healthy diet) with a non-randomized comparator arm (CAU). Participants interested in a dietary intervention are randomized (50:50) to either an ED or a healthy diet with randomization within each participating center. Randomization by means of minimization is performed, including sex and age as factors, resulting in four groups. Within each group, blocked randomization is used (block size eight). The non-randomized comparator arm includes children who are being treated with CAU. Researchers disclose the group allocation to parents via a sealed envelope. Participants, researchers and dieticians are aware of treatment allocation. Researchers who will code the behavior observation (see secondary outcomes) are blinded to group allocation and time of assignment.

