### Sample size and power

The justification of sample size is calculated based on the assumption of superiority: we assume that the ED is more effective than the healthy diet on the ordinal primary outcome respondership (i.e. five categories: full responder, partial responder, mixed responder, non-responder and deterioration). A clinically relevant outcome is defined as detecting twice as many full responders in the ED group than in the healthy diet group. Each dietary group includes 81 children. With this sample size and using ordinal regression, the power is 0.99 (α = 0.05, two sided test) to detect double the amount of full responders in the ED compared with the HD (Table 4: scenario 1). In addition, the power to detect one and a half times as many full responders in the ED compared with the healthy diet is 0.64 (α = 0.05, two sided test) (Table 4: scenario 2).

**Table 4 Tab4:** Hypothetical Distribution of Participants for Power Calculation

	Full responder	Partial responder	Mixed responder	Non-responder	Deterioration
Scenario 1					
Elimination diet	16 (20)	45 (55)	10 (12%)	6 (8%)	4 (5%)
Healthy diet	8 (10%)	24 (30%)	21 (25%)	16 (20%)	12 (15%)
Scenario 2					
Elimination diet	12 (15%)	37 (45%)	13 (16%)	11 (14%)	8 (10%)
Healthy diet	8 (10%)	24 (30%)	21 (25%)	16 (20%)	12 (15%)

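### The two analyses called moderator analyses group children by outcome, so they find predictors of response and adherence and cannot show which factors change the elimination-versus-healthy-diet effect

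*Protocol article*

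**What the plan says.** The objectives at the end of the Background state that "the study aims to identify potential moderators and mediators (e.g. socioeconomic status (SES), ethnicity, comorbidity) of the short- and long-term response to dietary treatments". The Discussion repeats the moderator part of this aim in similar terms.

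The Statistical analyses section then says what will be done. The first analysis is given as "Finally, two moderator analyses will be performed: one comparing dietary responders versus non-responders (predicting respondership", and the second as "another comparing children/families adhering to a dietary treatment versus children/families that are not able to do so (predicting adherence". On timing: "Both moderator analyses will be performed to compare children/families after 5 weeks and after 1 year of treatment".

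The design around these analyses is a randomized comparison of two diets. Under Randomization: "Participants interested in a dietary intervention are randomized (50:50) to either an ED or a healthy diet". The primary ordinal analysis is described as "comparing odds for reducing ADHD symptoms and emotion dysregulation symptoms in the elimination diet group with the corresponding odds in the healthy diet group". Under Sample size and power: "Each dietary group includes 81 children".

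**The concern.** In a two-arm randomized trial, a moderator of treatment effect is a baseline factor across whose levels the ED-HD difference varies. Detecting one requires the diet contrast within levels of the factor or, equivalently, a diet-by-factor term. The two stated analyses do something else. They sort children by what happened to them (responded or not, adhered or not) and ask which characteristics go with the better outcome. The article's own bracketed descriptions, which speak of prediction, confirm this.

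A factor that goes with improvement under any diet, for instance through natural improvement or parental expectation, would appear in such a comparison and be reported under the name of moderator. A clinician would probably take that as guidance on which children should be offered the more demanding ED rather than the HD. The randomized HD arm could supply that information, but the analyses as described do not use it.

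**Working it through.** **Plan's own figures.** The article gives no figure for the moderator analyses. Its power statements for the primary comparison reproduce when a rank test is simulated on Table 4 with 81 per arm: 0.992-0.994 against the stated 0.99 (scenario 1), and 0.625-0.645 against 0.64 (scenario 2). The sample size and rates are therefore a fair base for an illustration.

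**Inputs.**
- From Sample size and power: 81 per arm, two-sided α = 0.05.
- From Table 4, scenario 2: full plus partial responders are 10 + 30 = 40% in HD and 15 + 45 = 60% in ED.
- Assumed: response means full or partial responder; a binary baseline factor X is present in 50% of children; the X-specific response rates are as given below.

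**Step 1: X purely prognostic, with the same odds ratio in both diets, so no moderation.** Solve p1 = OR·p0/(1 − p0 + OR·p0) with (p0 + p1)/2 equal to 0.40 in HD and 0.60 in ED.
- OR 2: HD 31.8% and 48.2%; ED 51.8% and 68.2%.
- OR 3: HD 27.2% and 52.8%; ED 47.2% and 72.8%.

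Power ≈ Φ(|d|/SE − 1.96), with SE = √(2·p̄(1 − p̄)/m), where m is the number of children per level of X.
- Diets pooled, m = 81, p̄ = 0.50: SE = √(0.50/81) = 0.0786. OR 2: d = 0.1645, ratio 2.09, power 55%. OR 3: d = 0.2564, ratio 3.26, power 90%.
- ED only, m = 40.5, p̄ = 0.60: SE = √(0.48/40.5) = 0.109. OR 2: ratio 1.51, power 33%. OR 3: ratio 2.36, power 65%.
- Interaction test: the log odds ratios are equal in the two diets, so the test rejects at its nominal level, about 5%.

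Simulation agrees. Two independent runs gave 55% and 57% (OR 2) and 91% and 92% (OR 3) for the pooled comparison, 33% and 66% for ED only (one run), and 4-5% for the interaction. A stronger prognostic factor (HD 25% and 55%, ED 45% and 75%; diet odds ratio 2.45 at both levels) gave 97% pooled, 79% ED only and 5% interaction.

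**Step 2: X a true moderator.** For the interaction test, the estimate is the difference between the two within-diet log odds ratios, with variance Σ 1/[40.5·p(1 − p)] over the four cells. Example, first row below: ln(0.75/0.25) − ln(0.45/0.55) = 1.299 in ED and ln(0.30/0.70) − ln(0.50/0.50) = −0.847 in HD. The difference is 2.147, SE 0.669, ratio 3.21, power 89%. Simulated rejection rates:

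| ED rates (X absent, present) | HD rates (X absent, present) | Pooled | ED only | Interaction |
|---|---|---|---|---|
| 45%, 75% | 50%, 30% (opposite directions) | 9% | 80% | 90% |
| 50%, 70% | 50%, 30% (opposite directions) | 4% | 44% | 74% |
| 45%, 75% | 40%, 40% | 48% | 80% | 50% |
| 45%, 75% | 35%, 45% | 72% | 79% | 25% |
| 60%, 60% | 50%, 30% | 26% | 5% | 27% |

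**Reading.** The false-label result in Step 1 has the same direction whether or not the diets are pooled. The detection result in Step 2 depends on the assumed pattern. The interaction test has a clear advantage over the pooled comparison only in the two rows where X acts in opposite directions. Elsewhere it is no better, or is worse, at rejecting. What it retains is a specific meaning: it responds to a change in the ED-HD effect and not to prognosis.

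**The case against.** The strongest reply is that the stated aim concerns response to dietary treatments, not the ED-HD difference, and that the analyses are openly described as predicting respondership and adherence. On that wording they address the aim. This stands in part. A reader might infer that the aim will receive a wrong answer, but the documents do not go that far, because they never state an aim of moderating the ED-HD contrast. What remains is that a predictor analysis carries the name moderator in a randomized comparison of two diets, where that name invites the treatment-effect reading.

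Second, pooling is an inference; the article names neither a test nor a list of factors, and such detail may sit in the full protocol or analysis plan. This is also right. The point does not need pooling, since a within-ED comparison also flags a purely prognostic factor far above 5%. Nor is it a complaint about missing detail, since the article itself says which groups are compared.

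Three further inferences are not supported:
- That the deterioration group has no place in a two-way split. The section on the second phase puts it with the children who do not respond. Only the mixed responders are left unassigned, which a condensed article may leave to the fuller document.
- That SES and ethnicity are put forward as mediators. The objective gives one list of examples for moderators and mediators jointly and does not say which is which.
- That an interaction test would generally detect more true moderators. The table under the working shows that this depends on an assumed crossover, and nothing in the documents points to one.

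**Conclusion.** The point holds in this limited form. The two analyses identify predictors of respondership and of adherence, and reporting their results as moderators would mislabel prognostic factors. Under the stated assumptions (81 per arm, a binary factor in 50% of children, response as full or partial responder, overall rates near 40% and 60%), a factor with no moderating role is flagged in about 55-92% of trials with diets pooled and 33-66% within ED, against about 5% for an interaction test. The percentages move with the assumed odds ratio; the direction does not. No general claim about power to find true moderators follows. These are secondary analyses, and the primary ED-HD comparison is unaffected, but the correction is worth making because it changes what the trial may say about who gains from ED over HD.

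**What to change.** Rename the two present analyses as predictors of respondership and predictors of adherence, and report them under those names. Add exploratory moderator analyses: for each baseline factor named in advance, enter the factor and its product with diet (ED versus HD) in the ordinal model already planned, keeping all five response categories, and report the interaction odds ratio with its 95% confidence interval.

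The cost is a change of wording and a few extra models on data already to be collected. The drawback is limited power for interactions at N = 162 (25% to 90% across the assumed patterns above), so the results should be presented as estimates with their uncertainty, and a non-significant interaction should not be read as absence of moderation.
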